## Abstract

**Methods::**

Data will be collected from a prospective observational cohort study conducted in South Korea. Eighty participants with SCD aged ≥ 60 years are eligible for the study. All participants undergo annual neuropsychological tests and neurological examinations, bi-annual brain MRI scans and plasma amyloid markers, and baseline florbetaben Positron Emission Tomography scans. The amyloid burden and regional volumes will be measured. Cognitive and biomarker changes will be compared between the amyloid-positive SCD and amyloid negative SCD groups. Validation would be performed to assess reliability and feasibility of HCT.

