**Conclusions::**

This study would suggest a perspective on SCD in terms of cognitive and biomarker trajectories. Baseline characteristics and biomarker status might affect faster cognitive decline and future biomarker trajectories. In addition, HCT could be an alternative option of in-person neuropsychological tests to track cognitive changes without visiting hospitals.

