### 1.2. Study aims

The objective of this study is to assess whether amyloid-positive (A + ) SCD progress rapidly compared with amyloid negative SCD. Our second aim is to validate a newly developed HCT as an alternative cognitive monitoring tool without vising hospitals.

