### 2.7. Outcome measures

The primary outcome measure is K-MMSE score changes at the endpoint. The secondary outcome measures include demographic data, baseline and follow-up SNSB subdomain scores, self-report questionnaires, HCT scores, brain MRI markers, florbetaben PET positivity, quantitative regional amyloid depositions using PET scans, and clinical progression rates.

All participants will undergo baseline neurologic examinations, neuropsychological tests named SNSB, brain MRIs, blood labs, and florbetaben PET scans for amyloid depositions. PET findings are interpreted using a visual rating scale named brain amyloid plaque load and rated as positive amyloidosis with a brain amyloid plaque load score of 2/3.^[9]^ Quantitative neuroimaging analysis will be performed.

At baseline, questionnaires for SCD, amyloid PET scans, brain MRIs including 3 dimensional-T1 imaging, plasma amyloid beta values are examined. Telephone-based HCT at home are performed every 6 months during the study period. Annual follow-up evaluations include detailed neuropsychological tests, physical and neurologic examinations, and physician’s assessments for clinical progression. Brain MRI and plasma amyloid beta values are assessed at baseline and 24 months later (Table 1).

Clinical progression to mild cognitive impairment or dementia will be assessed at the final visit. The cognitive tests were administered by a trained neuropsychologist. Participants with CDR score ≥ 0.5 or Korean version of activities of daily living score ≥ 0.43 were considered to have progressed to MCI or dementia.

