### 2.11. Statistical analysis

Independent *t* test or nonparametric Mann–Whitney *U* test (based on normal distribution patterns) is used for comparison of continuous variables such as baseline demographics and clinical characteristics between A + SCD and A − SCD participants. Chi-square tests will be used to compare categorical variables between the 2 groups. analysis of covariance corrected for baseline scores would be used to compare cognitive changes between the 2 groups. All statistical analyses are performed using SPSS (version 18.0; SPSS Inc, Chicago, IL). *P* values < 0.05 is considered to indicate statistically significant differences.

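### The home-based cognitive test (HCT) is to be validated for reliability and feasibility, which does not support the stated aim and conclusion that it is an alternative to in-person tests for tracking cognitive change

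*Protocol article*

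**What the plan says.** - **Aim** (Section 1.2): "Our second aim is to validate a newly developed HCT as an alternative cognitive monitoring tool without vising hospitals".
- **Conclusion in view** (Abstract, Conclusions): "HCT could be an alternative option of in-person neuropsychological tests to track cognitive changes without visiting hospitals". The Discussion makes the same case for detecting change at home.
- **What the validation will assess** (Abstract, Methods): "Validation would be performed to assess reliability and feasibility of HCT". No other sentence in the article names a property to be validated.
- **Tests named** (Section 2.11): a t test or Mann–Whitney U test "is used for comparison of continuous variables such as baseline demographics and clinical characteristics between" amyloid-positive and amyloid-negative participants; "Chi-square tests will be used to compare categorical variables between the 2 groups"; and "analysis of covariance corrected for baseline scores would be used to compare cognitive changes between the 2 groups".
- **Data** (Section 2.7): "Telephone-based HCT at home are performed every 6 months during the study period". For the in-person side: "Annual follow-up evaluations include detailed neuropsychological tests, physical and neurologic examinations, and physician’s assessments for clinical progression". In Table 1, SNSB, which includes K-MMSE, is given at screening and at 12, 24, 36 and 48 months. HCT is given at baseline and at the same follow-up visits.

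**The concern.** An instrument offered as an alternative way of tracking change has to be shown to follow change. Reliability says that scores are reproducible. Feasibility says that the call can be made and completed. An instrument can have both and still fail to decline in people whose in-person performance declines.

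A group comparison does not fill the gap. If amyloid-positive participants lost more HCT points than amyloid-negative ones, that would not show that the individuals who worsen on HCT are those who worsen on K-MMSE or SNSB.

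If the stated scope is followed, one of the study's two aims could end with a favourable reliability coefficient and a high completion rate, and these would be read as support for monitoring at home. The question that matters to a clinic, whether a fall in HCT signals a fall on in-person testing or clinical progression, would be unanswered although the data to address it had been collected.

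**Working it through.** **Step 1. Set the claims beside the evidence.**

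| Claim or evidence | Where | Shows that HCT follows in-person change? |
|---|---|---|
| Alternative monitoring tool | Section 1.2 | This is the claim |
| Alternative to in-person tests for tracking change | Abstract, Conclusions | This is the claim |
| Reliability | Abstract, Methods | No: reproducibility only |
| Feasibility | Abstract, Methods | No: practicability only |
| t test, Mann–Whitney, chi-square, ANCOVA | Section 2.11 | No: differences between amyloid groups |

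**Step 2. Reproduce the article's own sample size.** Inputs from Section 2.10: difference 3.5 points, SD 4.5, alpha 0.05 (taken as two-sided), power 90%, discontinuation 10%.
- Normal approximation: n = 2 × (1.96 + 1.2816)² × 4.5² / 3.5² = 34.7, so 35 per group.
- The t-based version gives 35.7, so 36, as stated.
- 72 / 0.90 = 80, as stated.

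The calculation holds. It concerns the K-MMSE group difference only, so the precision available for HCT has to be worked out separately.

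**Step 3. Precision of a change correlation.** Completers: 80 × 0.90 = 72. With one change score per person, the 95% CI is tanh(atanh(r) ± 1.96/√(72 − 3)), where 1.96/√69 = 0.236. The values of r are assumptions, as the article gives none.
- r = 0.5: 0.30 to 0.66
- r = 0.7: 0.56 to 0.80
- r = 0.8: 0.70 to 0.87

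**Step 4. Number of progressors.** The Discussion gives 5–10% per year. Assume a constant annual rate over four years that applies equally to completers.
- 5%: 72 × (1 − 0.95⁴) = 72 × 0.1855 = 13.4
- 10%: 72 × (1 − 0.90⁴) = 72 × 0.3439 = 24.8

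That is about 13 to 25.

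**Step 5. Precision of discrimination.** Assume an AUC of 0.80 for HCT change against progression. Hanley–McNeil: Q₁ = 0.8/1.2 = 0.667 and Q₂ = 2 × 0.64/1.8 = 0.711, so Q₁ − 0.64 = 0.0267 and Q₂ − 0.64 = 0.0711.
- 13 vs 59: variance = (0.16 + 12 × 0.0267 + 58 × 0.0711)/(13 × 59) = 0.0060; SE 0.077; 95% half-width 0.15.
- 25 vs 47: variance = (0.16 + 24 × 0.0267 + 46 × 0.0711)/(25 × 47) = 0.0035; SE 0.059; 95% half-width 0.12.

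Both analyses are estimable from the planned data, with moderate precision.

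**The case against.** The strongest reply is that this is a condensed article. The reliability and feasibility wording is one abstract sentence and does not exclude other properties. Section 1.2 sets a broader task. Section 2.11 contains no reliability statistic either, so it evidently does not describe the HCT analysis at all, and a full protocol or analysis plan may hold one.

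Much of this stands. The silence of Section 2.11 about HCT would not be a finding on its own. What remains is a mismatch between statements the article does make: it names the properties to be validated, then names a conclusion that needs a different one. Those statements need aligning whatever an unseen document contains.

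It is also fair that HCT scores are a secondary outcome, that the abstract's conclusion is worded tentatively, and that the type of reliability is left open. Internal consistency of the 20 questions, for example, would need no repeat interval.

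**Conclusion.** The stated validation scope does not support the stated second aim and conclusion. This matters for the HCT claim alone. The sample size, the primary K-MMSE comparison and the data collection are unaffected. The mismatch itself rests on the wording and on no numerical assumption. The precision figures are illustrations that depend on the assumed correlations, the assumed AUC, 72 completers and a constant progression rate.

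A reader might infer more, but the documents do not support it:
- **That HCT is meant to replace in-person tests.** The article presents it as an alternative option, and in-person testing continues every year.
- **That the study cannot answer the question.** The limit lies in the stated analyses; the scheduled data can address it.
- **That the reliability estimate is already compromised by 6-month intervals, a narrow score range or a ceiling.** No reliability type, HCT score distribution or item difficulty is given. Entry selects on SNSB and CDR, not on HCT, and people with SCD are the intended users, so an estimate in this cohort is relevant to them.
- **That limits of agreement between HCT and K-MMSE are needed.** The article gives a 0–30 range for HCT and none for K-MMSE, and a shared maximum would not make the points interchangeable.

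**What to change.** In the abstract and Section 2.11, extend the HCT validation to validity for change, using visits already in Table 1:

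1. **Association of change.** Estimate the within-person association of HCT change with K-MMSE change, and with SNSB scores, over the paired screening/baseline, 12-, 24-, 36- and 48-month assessments. Use a mixed model or repeated-measures correlation and report a 95% CI. Note that the first pair is slightly offset, because SNSB is given at screening and HCT at baseline.
2. **Discrimination.** Report how well HCT change separates participants who progress under the CDR/ADL rule in Section 2.7 from those who do not, with its CI and the number of progressors.

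Keep reliability and feasibility as supporting properties. Make the alternative-to-in-person claim only if both analyses support it. If they are not to be added, limit the HCT conclusion in the abstract and Discussion to reliability and feasibility. Fix the choice before the 48-month data are analysed, so that the validation measure is not picked after the results are known.

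The cost is a change of wording and a little more analysis work, with no new visits, participants or procedures. The drawback is that the HCT claim may prove weaker and carry a wide interval.

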**Conclusions::**

This study would suggest a perspective on SCD in terms of cognitive and biomarker trajectories. Baseline characteristics and biomarker status might affect faster cognitive decline and future biomarker trajectories. In addition, HCT could be an alternative option of in-person neuropsychological tests to track cognitive changes without visiting hospitals.

## 1. Introduction

### 1.1. Background

Subjective cognitive decline (SCD) indicates a self-perceived persistent cognitive worsening despite of normal performance in standard neuropsychological tests.^[1]^ SCD is regarded as a risk group of dementia and Alzheimer’s disease (AD) and important as a target population for secondary preventions.^[2,3]^ However, due to its heterogeneity and uncertainty regarding future cognitive trajectories and underlying pathologies, SCD is not identical with preclinical stages of AD. Considering that subjects with SCD progress slowly, regular cognitive monitoring to assess clinical progressions in outpatient clinics are practically difficult. After worldwide pandemic of coronavirus 19, patients are more reluctant to vising hospitals. Therefore, baseline biomarker evaluations to predict faster cognitive declines and regular cognitive monitoring of the high-risk patients are clinically important.

We planned a cohort based longitudinal observational study to develop a home-based cognitive test (HCT) and assess cognitive and biomarker trajectories of SCD according to baseline biomarker status.

### 1.2. Study aims

The objective of this study is to assess whether amyloid-positive (A + ) SCD progress rapidly compared with amyloid negative SCD. Our second aim is to validate a newly developed HCT as an alternative cognitive monitoring tool without vising hospitals.

## 2. Methods

### 2.1. Study design

This study is a longitudinal observational cohort based study performed at a university-affiliated dementia clinic from May 2020 to December 2025. A total of 80 elderly participants with SCD who presented with a complaint of persistent cognitive decline are planned to be enrolled at baseline in a single center and undergo annual follow up evaluations during 48 months (see Table 1).

**Table 1 T1:** Data collection.

Assessments	Screening	Baseline	12/36 months	24 months	48 months
Eligibility	**√**				
Demographics	**√**				
Comorbidity	**√**	**√**			
Concomitant medication	**√**	**√**	**√**	**√**	**√**
Blood chesmistry	**√**				
Plasma amyloid beta		**√**		**√**	
SNSB	**√**		**√**	**√**	**√**
Self-report questionnaire		**√**	**√**	**√**	**√**
Brain MRI	**√**			**√**	
Florbetaben PET		**√**			
Physical examination	**√**	**√**	**√**	**√**	**√**
Vital signs		**√**	**√**	**√**	**√**
Neurologic examination	**√**	**√**	**√**	**√**	**√**
HCT*		**√**	**√**	**√**	**√**
Physician’s judgements of progression			**√**	**√**	**√**

HCT = home-based cognitive test, PET = positron emission tomography, SNSB = Seoul neuropsychological screening battery.

* Home-based cognitive tests (HCT) are performed every 6 months during the study period.

First, we have developed a HCT (score range 0–30, higher scores indicate better cognitive function) composed of 20 questions that can be assessed using phone-calls. Second, neuropsychological tests, blood samplings, physical and neurologic examinations, brain MRIs, florbetaben positron emission tomography (PET) scans, self-report questionnaires are evaluated at baseline. Third, all participants undergo annual follow up neuropsychological tests, physical and neurologic examinations, physician’s history taking to judge clinical progression. All participants should undergo bi-annual brain MRI scans and plasma amyloid beta markers until the end of the study (Table 1). The first participant was enrolled in June 2020, and remaining participants are being recruited.

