### 2.10. Sample size calculation

We assumed that a 3.5-point difference in K-MMSE assessment scores (the primary outcome measure between the A + SCD and SCD groups) after 48 months would be significant. With an alpha value set at 0.05, a beta value of 0.9 (90% power), and a SD value of 4.5 for change, a total of 36 participants were required for each study group. Assuming a discontinuation rate of 10% during the 48-month study, the total calculated sample size required for the study was 80 participants.

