## 3. Discussion

In this study, we aim to conduct a longitudinal observational study to assess cognitive and biomarker changes in Korean participants with SCD over the course of 48 months. We will assess whether SCD participants showed different cognitive and biomarker trajectories according to biomarker status. We hypothesize that A + SCD participants would show more cognitive decline and atrophic changes after 48 months. Baseline neurodegenerative changes and amyloid burden are expected to be related with cognitive trajectories in SCD. In particular, neurodegenerations combined with sufficient amyloid depositions above the threshold level would show rapid cognitive progression in SCD participants because existence of the 2 key pathologies indicate later stages of preclinical AD. In addition, in an effort to monitor cognitive declines in SCD participants, we have developed a new HCT as an alternative option of hospital-based in-person neuropsychological tests. Considering that subjects with normal cognition are still reluctant to visiting hospitals for regular in-person cognitive tests and this population generally show lower annual progression rates (5–10% annually) compared with those with MCI/ dementia,^[2,3,17]^ regular cognitive monitoring at home would be clinically helpful to detect cognitive changes in SCD subjects without visiting hospitals for the cognitive tests.

We are now conducting recruitments of the participants and baseline database will be completed by 2023. Despite of a few limitations that other biomarkers assessing combined tau, alpha synuclein, or TAR DNA-binding protein 43 pathologies are not evaluated, our study have several strengths as followings: Participants are consecutively recruited in South Korea using a comprehensive neuropsychological test battery and undergo various biomarker evaluations, allowing us to clarify cognitive and biomarker trajectories of SCD participants. All participants undergo baseline amyloid PET scans, regular brain MRI scans, and plasma amyloid beta markers to quantitatively measure amyloid burden and neurodegenerative changes.

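### The December 2025 study end allows a 48-month K-MMSE score only for participants enrolled by December 2021, while recruitment is described as open and baseline completion is given as 2023; the 10% loss allowance does not cover this truncation

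*Protocol article*

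**What the plan says.** All statements are in the protocol article.

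- Section 2.1 (Study design) places the study at a single centre, "performed at a university-affiliated dementia clinic from May 2020 to December 2025". Participants "undergo annual follow up evaluations during 48 months".
- The same section gives the recruitment status: "The first participant was enrolled in June 2020, and remaining participants are being recruited".
- Section 3 (Discussion) adds: "We are now conducting recruitments of the participants and baseline database will be completed by 2023".
- Section 2.7 (Outcome measures): "The primary outcome measure is K-MMSE score changes at the endpoint". Section 2.10 (Sample size calculation) sets the planning difference at 3.5 points after 48 months, with SD 4.5 for change, alpha 0.05 and 90% power. This gives 36 per group.
- Section 2.10 then reaches a total of 80: "Assuming a discontinuation rate of 10% during the 48-month study".
- Table 1 schedules the SNSB, which contains the K-MMSE (Section 2.6), at 12, 24, 36 and 48 months.

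The article gives no last-enrolment date, no number enrolled to date, no shorter follow-up for late entrants and no extension beyond December 2025.

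**The concern.** The endpoint takes four years to reach, so the study end date fixes the last useful enrolment date. Counting 48 months back from December 2025 gives December 2021. The article describes recruitment as still open and places completion of the baseline data at 2023. On the natural reading, some participants enter after December 2021.

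Each of them would be cut off by the calendar before month 48. That loss is separate from discontinuation, which is all the 10% allowance is said to cover. What is at stake is the power of the primary comparison. There is also a risk to its meaning: if a late entrant's last available score were taken as the endpoint value, changes over different lengths of follow-up would be mixed in a comparison planned at 48 months.

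**Working it through.** **Inputs.** From Section 2.10: difference 3.5, SD of change 4.5, alpha 0.05, power 90%, 36 per group, 10% discontinuation, total 80. From Section 2.1: first enrolment June 2020, study end December 2025, 48 months of follow-up. The article does not say whether alpha is one- or two-sided; two-sided reproduces its figure.

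**Step 1: reproduce the plan's figure.** The normal approximation gives n per group = 2 × (1.960 + 1.282)² × 4.5² / 3.5² = 34.7, so 35. With the t distribution (noncentral t), 35 per group gives power 0.894 and 36 gives 0.902, so 36 per group. Then 72 / 0.90 = 80. The stated sample size reproduces. (One-sided alpha would give 29 per group by the normal approximation, which does not match.)

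**Step 2: slack.** 80 × 0.90 = 72 = 2 × 36. Nothing is left for any other kind of loss.

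**Step 3: last workable enrolment month.** December 2025 − 48 months = December 2021. June 2020 to December 2021 inclusive is 7 + 12 = 19 months of accrual.

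**Step 4: share able to reach month 48.** The accrual pattern is not given. Assume uniform accrual from June 2020 over m months, so the share is 19 / m. Apply the planned 10% discontinuation to those who can reach month 48, keep the article's equal groups, and compute two-sided power by noncentral t with difference 3.5 and SD 4.5.

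| Accrual ends | m (months) | Can reach month 48: 80 × 19/m | Cut off by the end date | Completers: × 0.9 | Power, no discontinuation | Power, 10% discontinuation |
|---|---|---|---|---|---|---|
| Dec 2021 | 19 | 80 | 0% | 72 | 93.0% | 90.2% |
| Mar 2022 | 22 | 69.1 | 14% | 62.2 | 89.0% | 85.5% |
| Jun 2022 | 25 | 60.8 | 24% | 54.7 | 84.7% | 80.6% |
| Dec 2022 | 31 | 49.0 | 39% | 44.1 | 76.0% | 71.4% |
| Jun 2023 | 37 | 41.1 | 49% | 37.0 | 68.1% | 63.3% |
| Dec 2023 | 43 | 35.3 | 56% | 31.8 | 61.2% | 56.5% |

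**Step 5: thresholds.** Truncation alone exceeds 10% once more than 8 of 80 are enrolled after December 2021. Under uniform accrual this happens when m > 19 / 0.9 = 21.1 months, that is, when accrual runs past about February 2022. If the planned 10% discontinuation also occurs, any truncation takes the evaluable number below 72.

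**Step 6: follow-up of those cut off.** If accrual ends in December 2022, everyone cut off can still have a month-36 visit. If it ends in December 2023, the latest entrants have only 24 months.

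**The case against.** The strongest reply is that the 2023 date is a milestone for the baseline database, not for the last enrolment. Completing that database may include PET and MRI quantification, plasma assays and data entry after the last participant has entered, and the wording can also mean before 2023 begins. The statements that recruitment is open are not dated in the text. Enrolment finished by December 2021, a baseline database finished later and month-48 visits by December 2025 would be compatible. This stands. A reader might infer that the three dates cannot all hold, or that the 10% assumption fails, but the article proves neither, because it does not say how many entered after December 2021. If at least 72 had entered by then, truncation alone would stay within 10%. With 60 entered by then and 10% discontinuation, 54 would complete and power would be 80%.

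A reader might also be tempted to add an unequal amyloid split, which lowers power further. The documents give no amyloid-positive share and plan equal groups, so any such loss is a different issue and is left out here.

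It is also fair to say that no passage substitutes an earlier score for month 48, and that the handling of truncated follow-up may be set out in an analysis plan that is not shown. The point therefore does not rest on missing analysis detail. It rests on dates the article states and on an allowance worded as discontinuation only. An analysis plan could limit the damage but could not supply month-48 scores after the study has ended.

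**Conclusion.** The concern holds as a conditional conflict of dates. The stated end allows the 48-month primary outcome only for participants enrolled by December 2021, and the article's account of recruitment points to later enrolment without stating it. Each later entrant is an extra loss that the 10% does not cover, in a sample size with no slack. The sample size calculation itself is correct for 72 completers.

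The size is uncertain. With uniform accrual from June 2020, equal groups and 10% discontinuation, power falls from 90% to 85.5% for accrual ending in March 2022, 80.6% for June 2022, 71.4% for December 2022 and 56.5% for December 2023. The last of these takes the latest reading of the 2023 date. Faster early accrual makes the loss smaller, and it is zero if all 80 were enrolled by December 2021.

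**What to change.** Reconcile the dates in Sections 2.1 and 3: state the last-enrolment date, actual or planned, and set the study end at 48 months after the last participant's baseline.

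If December 2025 is fixed, make two changes:

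- Restate the power in Section 2.10 for the number of participants who can reach month 48, with discontinuation applied on top.
- Use the annual K-MMSE scores already scheduled in Table 1, for example in a mixed model that estimates the between-group difference at 48 months. Participants cut off early then contribute the visits they have. State that no earlier score stands in for month 48.

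The cost is a later study end in the first case. In the second it is a less favourable stated power and slightly more analysis work. Neither adds a visit to the schedule. If all 80 were in fact enrolled by December 2021, one sentence saying so settles the point.
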